### Participant recruitment and study procedure

Patients admitted in emergency department (ED) with suspected gastric or duodenal perforation based on clinical and radiological assessment will be evaluated for eligibility and considered as possible candidates for the study.

Routine pre-operative management for GDP will be done for all patients including; taking vital signs like; Blood pressure (BP), pulse rate (PR) respiratory rate (RR), oxygen saturation (SPO2) and temperature plus continuous monitoring, passing Foley’s urethral catheter and monitoring urine output, passing two large bore cannulas, fluid resuscitation with IV Normal saline till urine output is >0.5 mls/h, nasogastric tube insertion, nil by mouth, intravenous (IV) ceftriaxone 2 grams (g), IV metronidazole 500 milligrams (mg), IV Paracetamol 1g, IV omeprazole 40 mg, doing complete blood count (CBC), doing blood grouping and cross match, serum electrolytes, and obtaining informed consent for emergency laparotomy.

After resuscitation, the patients will be taken for laparotomy under intubation general anesthesia. Patient’s particulars will be recorded in the data collection form including participant identification number (PIN), age, address, presenting symptoms and duration of symptoms among others as shown in appendix I. The type of perforation surgery will be recorded.

Post operatively patients in both groups will receive all the routine post-operative care. This will include IV Normal saline and 5% dextrose in the ratio of 2:1, which will be prescribed for the first 24 hours with the total volume determined by the 4:2:1 rule for calculating maintenance fluids. The fluid prescriptions that follow, will be according to fluid balance chart. Other post-operative instructions will include; IV ceftriaxone 2g once a day (OD) for 5 days, IV metronidazole 500mg 8 hourly for 5 days, IV Omeprazole 40mg OD till oral feeding is initiated, IV Paracetamol 1g 8 hourly till oral feeding is initiated, Oral warm water will be started on first POD, early removal of NGT will be done, ambulation will be encouraged from first POD [14,25]. In addition to the above, patients in group A will receive chewing gum and below is a clear instruction on how they will use it. Figure 1 shows a flow chart summarizing the study procedure.

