### Eligibility criteria

#### Inclusion Criteria

All patients with confirmed gastric or duodenal perforation, between the age of 18 and 65 will be included. The upper age limit will be used because increasing age increases the risk of PPOI [10] yet we want the groups to be comparable.

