### Sampling technique, randomization, concealment allocation and blinding

Permuted balanced block randomization will be conducted by the study supervisor to generate a random sequence of numbers to represent the two groups in an equal allocation ratio of 1:1. The random numbers will be labeled on concealed envelopes. The sealed envelopes will contain a folded opaque paper with letter A or B representing (chewing plus routine care) and (non-chewing plus routine care) groups respectively so that its not possible to deduce the assignment group based on random sequence numbers by the allocating team (research assistants). In addition, the envelope will have a similar stamp on the seal to be able to deduce possibility of breach of protocol (premature opening of the envelope). At this time both consent for surgery, information about the study and or consent to participate in the study will be obtained in writing at the emergency department. This is to avoid bias of recruiting participants after knowledge of intra-operative findings and to enable pre-operative care standardization between groups. The allocating team (trained research assistants) will give the envelope to the eligible participant 2 hours prior to surgery when a diagnosis of gut perforation is made from the radiological findings. The envelope will remain sealed until the patient enters the operating room and the participant will be unblinded just before induction of anesthesia where an instruction will be issued regarding chewing or not chewing any gum post-operatively. At this point an additional number either H, F or K will be added to the sequence number on the envelope to form participant identification number (PIN) to represent HRRH, FRRH, KIUI-TH for tracking records of recruitment and representation from each hospital. The outcome assessors (attending physicians) will be blinded throughout about the ongoing study since chewing gum is not known to cause adverse effects that would warrant un-blinding. The recruiting team will be totally different from the outcome assessors.

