**Figure 1 F1:**
[figure not shown]
Flow chart for sampling and data collection procedure.

Any breach or failure to adhere to pre or post-operative protocol will lead to termination of the individual participants from the RCT. Adherence to the trial protocols will be checked for in the patients’ treatment record charts from the time of admission to the end of the follow-up period.

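### The pre-operative urine-output target is printed as more than 0.5 mL per hour with no body-weight term (12 mL a day), so it cannot work as a resuscitation endpoint

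*Protocol article*

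**What the plan says.** The section Participant recruitment and study procedure lists the routine pre-operative care that all patients receive. Within that list, saline is to be given to a urine-output endpoint: "fluid resuscitation with IV Normal saline till urine output is >0.5 mls/h". The output is to be measured by catheter, and other signs are to be followed: "oxygen saturation (SPO2) and temperature plus continuous monitoring, passing Foley’s urethral catheter and monitoring urine output". Blood pressure, pulse, respiratory rate and serum electrolytes are also listed. None of these other items carries a numeric goal. The remaining numbers in the pre-operative list are drug doses and the count of cannulas.

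The next paragraph moves to surgery: "After resuscitation, the patients will be taken for laparotomy under intubation general anesthesia".

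Two other places bear on the consequences. The section on randomisation and blinding states: "The envelope will remain sealed until the patient enters the operating room". The text below the Figure 1 caption states: "Any breach or failure to adhere to pre or post-operative protocol will lead to termination of the individual participants from the RCT".

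**The concern.** The printed figure is an hourly volume with no reference to body weight. For adults aged 18 to 65 (Inclusion Criteria), half a millilitre an hour is close to no urine at all, and almost any measurable output through a catheter would exceed it. A threshold that nearly every patient passes gives no information on whether resuscitation is adequate.

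What is at stake is patient care as the protocol describes it. The patients have perforations and are about to have an emergency laparotomy. The urine figure is the stated point at which saline resuscitation stops, and surgery comes next. Followed literally, it would let a patient with almost no urine output go to theatre as resuscitated. It also weakens the pre-operative protocol as a standard for checking charts at three hospitals: a reviewer using the printed number would pass nearly everyone, and one who reads in a per-kilogram term would be applying a standard that the document does not state.

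**Working it through.** **Inputs from the protocol article**
- Printed target: more than 0.5 mL/h, no weight term (Participant recruitment and study procedure).
- Post-operative fluids for the first 24 hours: "total volume determined by the 4:2:1 rule for calculating maintenance fluids" (same section). This is a weight-based rule, used here only for scale.

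**Inputs that are assumptions**
- Body weight of 50 to 80 kg. The document gives no weights.
- An intended target of 0.5 mL/kg/h. The document does not say this.

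The protocol gives no derivation of the 0.5 figure, so there is nothing to reproduce. The check is one of units.

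**Step 1. The printed target as a daily volume**

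0.5 mL/h × 24 h = 12 mL a day, at any body weight.

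**Step 2. The printed target per kilogram**

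Printed rate ÷ weight:
- 50 kg: 0.5 / 50 = 0.010 mL/kg/h
- 80 kg: 0.5 / 80 = 0.00625 mL/kg/h

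**Step 3. The target if a per-kilogram term was dropped**

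Target = 0.5 mL/kg/h × weight; daily volume = target × 24 h.

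| Assumed weight | Target | Daily volume | Multiple of printed target |
|---|---|---|---|
| 50 kg | 25 mL/h | 600 mL | 25 / 0.5 = 50 |
| 60 kg | 30 mL/h | 720 mL | 30 / 0.5 = 60 |
| 70 kg | 35 mL/h | 840 mL | 35 / 0.5 = 70 |
| 80 kg | 40 mL/h | 960 mL | 40 / 0.5 = 80 |

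The last column equals the assumed weight by construction. It shows the size of the discrepancy but is not separate evidence of what was intended.

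**Step 4. Scale against the protocol's own fluid rule**

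On its usual reading, the 4:2:1 rule gives 4 mL/kg/h for the first 10 kg, 2 for the next 10 kg and 1 for each further kilogram: 40 + 20 + (weight − 20) mL/h.
- 50 kg: 40 + 20 + 30 = 90 mL/h, and 0.5 / 90 = 0.56%
- 80 kg: 40 + 20 + 60 = 120 mL/h, and 0.5 / 120 = 0.42%

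The printed urine target is therefore about half of one per cent of the maintenance fluid the same section prescribes after surgery. The rule also shows that the authors set fluids by weight elsewhere in this section.

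**Step 5. Effect on the comparison**

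The target applies before surgery to both arms. Allocation is disclosed only in the operating room, after resuscitation, so staff cannot apply the target differently by arm through knowledge of allocation. It does not enter the sample size, the primary outcome or the analysis.

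**The case against.** The strongest reply is that this is a copy-editing slip in routine care common to both arms. Operations are done under the supervision of general surgeons (Study setting), several other signs are monitored, and no experienced team would accept 12 mL a day as adequate. All of that is fair, and it is why the point is minor. It does not make the printed instruction right.

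A second reply is that a journal article condenses a fuller protocol, that the pre-operative list is not presented as exhaustive, and that Figure 1 and the data collection form cannot be seen here. The absence of numeric goals for blood pressure or pulse is indeed no fault, and a correct value may exist elsewhere. But this is a specific value stated wrongly, not a detail left out, and a correct figure elsewhere would still leave this sentence in error.

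Third, the intended value is not in the document. That stands: the evidence shows that the printed unit is implausible, not what should replace it.

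Fourth, the termination rule for protocol breaches adds little. Any patient resuscitated to 0.5 mL/kg/h also exceeds 0.5 mL/h, so clinicians following the probable intention would not fail the printed threshold, and nobody would be removed from the trial on that ground. This is accepted. The fault in an adherence check runs the other way: the printed threshold would pass patients it should not.

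**Conclusion.** The concern holds, as a minor point. The unit is wrong as written, and the only numeric resuscitation target before laparotomy does not separate an adequately resuscitated patient from one passing almost no urine. That conclusion needs only the printed figure and is held with high confidence.

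The size of the gap, a factor of 50 to 80, rests on two assumptions: that 0.5 mL/kg/h was meant, and that patients weigh 50 to 80 kg. The practical risk is limited by clinical supervision and the other monitoring. There is no effect on the validity of the treatment comparison.

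**What to change.** Ask the sponsor's clinicians to confirm the intended urine-output target. Then correct the unit in Participant recruitment and study procedure to an hourly rate per kilogram, for example more than 0.5 mL/kg/h if that is what was meant. If Figure 1, the data collection form or any site instruction repeats the printed figure, correct it there too.

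This is a one-line change. It adds no patients, procedures or analyses.

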**Figure 1 F1:**
[figure not shown]
Flow chart for sampling and data collection procedure.

Any breach or failure to adhere to pre or post-operative protocol will lead to termination of the individual participants from the RCT. Adherence to the trial protocols will be checked for in the patients’ treatment record charts from the time of admission to the end of the follow-up period.

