### Chewing gum administration

Green PK brand of chewing gum will be used in this study since a pilot survey done before data collection showed that majority of the people preferred the green flavor (*appendix II, unpublished data*). We will use one flavor to minimize bias. The patients in Group A will be given green flavored PK and will start chewing after regaining consciousness. The patients will chew 2 pellets of PK till they are tasteless three times in a day (morning, afternoon, and evening). After chewing, the patients will be encouraged to rinse the mouth with clean water. The patients will stop chewing gum when POI resolves. Resolution of POI will be defined as passage of stool or flatus or both in addition to full filling the criteria defined in the 6 domains described by the Tripartite gastrointestinal recovery post-operative ileus group such as absence of nausea and vomiting, having no need of nasogastric intubation, absence of abdominal pain and distension, and ability to tolerate oral feeds [29]. Each patient will be offered a watch, notebook, and pen and with the help of the caretaker, record every day’s events and the time they occur. The events recorded will include; time when gum is chewed, flatus passed, stool passed, vomited or hunger felt. The outcome assessors will do clinical evaluation 6 hourly and information will be recorded in the data collection form (appendix I).

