### Study variables

Primary outcome variable will be time taken from end of surgery to resolution of ileus.

Secondary outcome variables will be duration of hospital stay in days (counted from time of admission to time of discharge), in-hospital morbidity and mortality.

Morbidity will be defined as any deviation from the postoperative course that is not inherent in the procedure and does not comprise a failure of cure and will be reported in accordance with the Clavien Dindo classification 2004 [30]. Grade I: Any complication that does not require additional pharmacological, radiological or surgical intervention, II: Requires pharmacological treatment but not radiological or surgical intervention eg blood transfusion, III: Requires radiological or surgical re-intervention eg endoscopy and IV: Life threatening complications eg atleast one organ failure requiring ICU admission.

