### Data processing and analysis

The intention to treat model will be used during analysis to minimize bias. Summarized data will be analyzed using Statistical Package for the Social Sciences (SPSS Inc., Chicago, USA, version 22.0 for Windows). Continuous variables will be presented as the mean ± standard deviation. Categorical variables will be expressed as frequencies.

To compare the time taken for post-operative ileus to resolve and length of hospital stay, normality of distribution will be assessed using the Shapiro-Wilks test. If the data are found to be normally distributed, then equal variance for the two groups will be determined using Levene’s test hence two sample t-test will be computed assuming equal or unequal variance as appropriate. If the data are not normally distributed in both groups, the nonparametric Wilcoxon Rank sum (Mann-whitney U) test will be used to compare the difference in means. To compare the in-hospital morbidity and mortality, the chi squared test will be used. All analyses will be performed at 95% confidence level and a p value ≤0.05 will be considered significant.

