### Termination from the study

Individual participants will be terminated from the study if they do not adhere to protocol for instance cross-over to cause contamination, breach allocation or are lost to follow-up.

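### Terminating every participant who departs from the protocol contradicts the promised intention-to-treat analysis and can leave randomised patients without a primary outcome

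*Protocol article*

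**What the plan says.** Three statements in the protocol article's Methods bear on the same patients.

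- Below Figure 1, at the end of *Participant recruitment and study procedure*: "Any breach or failure to adhere to pre or post-operative protocol will lead to termination of the individual participants from the RCT". Adherence is checked in the treatment charts "from the time of admission to the end of the follow-up period".
- The section *Termination from the study* repeats the rule with examples: "Individual participants will be terminated from the study if they do not adhere to protocol for instance cross-over to cause contamination, breach allocation". Loss to follow-up stands in the same list.
- The section *Data processing and analysis* sets the analysis population: "The intention to treat model will be used during analysis to minimize bias".

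The outcome at risk is defined under *Study variables*, as follows: "Primary outcome variable will be time taken from end of surgery to resolution of ileus". It is established from six-hourly clinical evaluations and a patient diary (*Chewing gum administration*).

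**The concern.** Intention to treat exists to keep patients who deviate or cross over in the arm to which they were allocated. The termination rule removes those same patients from the trial. The article states both rules and nothing in it reconciles them.

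If termination stops follow-up, the time to resolution is never observed. The planned t-test or Mann-Whitney test needs an observed time for each patient, so calling the analysis intention to treat cannot restore it. In-hospital morbidity, mortality and length of stay would be lost for the same patients. The groups compared would then no longer be the groups that were randomised.

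The loss need not be random. Departures from routine care and cross-over can occur in either arm. Stopping or missing gum can occur only in the gum arm. If the gum patients removed are slow recoverers, the result favours gum. If more slow controls are removed, it favours control.

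**Working it through.** **Timing, from the text.** The envelope is given two hours before surgery and opened just before induction (*Sampling technique, randomization, concealment allocation and blinding*). Every post-operative departure therefore comes after allocation. Adherence is judged to the end of follow-up, while the primary outcome starts at the end of surgery and is complete only when ileus resolves. Termination can fall in between.

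**Which departures count.** Both arms can fail on routine care, since "patients in both groups will receive all the routine post-operative care" and some items are fixed, such as five days of named antibiotics and oral water on the first day. Both arms can cross over. Only the gum arm can miss gum.

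**Number removed (assumption).** The article gives no termination rate. For illustration I take the 10% added under *Sample size estimation*, although the article does not call it a dropout allowance: 52 - 52/1.1 = 4.7, about 5 of 52.

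**Case (a): removal unrelated to recovery.** There is no bias, and false gum benefit stays at 2.5%. With 24 v 23 analysed in place of 26 v 26, the ratio of standard errors is √[(1/24 + 1/23)/(2/26)] = √(0.0851/0.0769) = 1.05, so the interval is about 5% wider.

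**Case (b): removal at random from the slower half of the arm.** I simulated 200,000 trials with 26 v 26 standard normal times, no true effect, a pooled two-sample t-test at two-sided 0.05, and 5 patients removed in total. Negative shifts favour gum.

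| Removed, gum:control | Shift in difference (SD) | False gum benefit | False control benefit |
|---|---|---|---|
| 5:0 | -0.18 | 8.4% | 0.4% |
| 4:1 | -0.11 | 5.1% | 0.8% |
| 3:2 | -0.04 | 3.0% | 1.6% |
| 2:3 | +0.04 | 1.6% | 3.0% |
| 1:4 | +0.11 | 0.8% | 5.1% |
| 0:5 | +0.18 | 0.4% | 8.4% |

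The false control column is the mirror image of the false gum column.

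Hand check of the shifts: in samples of 26, the slower 13 average about 0.77 SD above the mean (from the simulation). Removing k of them moves the arm mean by -0.77k/(26 - k).

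- 5:0: -0.77 × 5/21 = -0.18.
- 4:1: -0.77 × 4/22 + 0.77 × 1/25 = -0.14 + 0.03 = -0.11.
- 3:2: -0.77 × 3/23 + 0.77 × 2/24 = -0.100 + 0.064 = -0.04.

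**Gum sessions.** Gum is due three times a day, and "The patients will stop chewing gum when POI resolves". Resolution at 2 days means about 6 sessions, and at 4 days about 12. With an assumed miss rate p per session, the chance of at least one failure is 1 - (1 - p)^(3 × days).

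- p = 0.01: 1 - 0.99^6 = 5.9% at 2 days; 1 - 0.99^12 = 11.4% at 4 days.
- p = 0.02: 1 - 0.98^6 = 11.4% at 2 days; 1 - 0.98^12 = 21.5% at 4 days.

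At these rates, if one missed session counts as a breach, a gum patient who takes twice as long to recover has nearly twice the chance of being terminated.

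**The case against.** **Termination may mean only that the intervention stops.** The article nowhere says that outcome data are discarded, and its one statement on who is analysed is intention to treat. That is fair, and the harm is conditional on termination ending follow-up. But patients are said to leave the trial itself and are listed beside those lost to follow-up. A site following that text could reasonably stop collecting data. A later analysis plan cannot recover outcomes that were never collected, so this is not detail that can be left to one.

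**Routine care already leaves room for judgement.** Later fluids follow the balance chart, nasogastric tube removal has no deadline, and ambulation is only encouraged. This stands in part: keeping a tube in is not clearly a breach. The antibiotics and first-day oral water are fixed, however, and the rule covers any departure. The exclusion of patients unable to chew after 24 hours covers one clinical reason for withholding gum, but it too takes effect after allocation.

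**The gum-session argument is thin.** It needs a single missed session to trigger termination, and the miss rates are invented. Adherence is checked in treatment charts while gum times go into the patient's notebook, so some misses may go unseen. All of this stands. The argument shows how removal could follow slow recovery, not how often it would.

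**The error rates are illustrative and mostly modest.** Adding the two directions gives a total error of 3.0% + 1.6% = 4.6% at 3:2, 5.1% + 0.8% = 5.9% at 4:1, and 8.4% + 0.4% = 8.8% only at 5:0. This is correct. The total hides the shift in the estimate, but the case for change rests on the contradiction in the text and not on these figures.

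**Conclusion.** The concern holds. The article contains a termination rule, stated twice and without exceptions, that conflicts with its own intention-to-treat commitment. Followed as written, it can leave randomised patients without a primary outcome.

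The size and direction of the net bias are not known. With 5 of 52 removed, the illustrations run from no bias, through ±0.04 SD for a near-even split of slow recoverers, to ±0.18 SD if all five come from one arm. They rest on assumptions about the number removed, the split between arms, the link to slow recovery and normality; the gum-session figures also rest on assumed miss rates. The point should be corrected; confidence is medium because the harm depends on how sites apply the word termination.

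**What to change.** In the paragraph below Figure 1 and in the section *Termination from the study*, replace termination with recording the deviation or, where relevant, stopping the gum. State that every randomised patient, including those who cross over, stop gum or have it held for clinical reasons, is followed to ileus resolution and discharge and analysed in the allocated arm. A per-protocol analysis may be added as a sensitivity analysis.

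The cost is wording in two places and no extra patients. The six-hourly evaluations and discharge date are already planned for inpatients and would simply continue for those who deviate. The downside is that cross-over patients kept in their allocated arm dilute the estimated effect; the per-protocol sensitivity analysis can show how much this may matter.
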